#### Setting

The trial protocol will be implemented and evaluated in two selected TB centres (within the premises of district hospitals) in the public sector which are designated TB diagnostic centres by the National TB Control Programme (NTP), and serve both rural and urban settings in two districts of the province of Punjab-Pakistan. These centres are routinely staffed by a doctor, designated TB facilitator and a laboratory technician. They are also equipped with a basic microbiology laboratory for sputum smear microscopy. These TB centres are busy out-patient settings and on an average deals with about 75-100 patients a day with limited human resource. A TB suspect is screened by the doctor (trained by NTP on TB case management protocols) supported by investigations and if diagnosed as TB case is registered by the TB facilitator (a paramedic trained on TB case recording and reporting) and offered six months of TB treatment. The follow-up of the case is also the responsibility of the doctor and the TB facilitator.

#### Study design and sample

The design of the trial is an individual randomised controlled trial (RCT). Figure 3 represents the overall flow of the events in the trial. To deliver 'Smoke Free Home’ intervention, the eligible non-smoking TB patients will be randomised and allocated to one of the two trial arms. **Arm 1** consists of “individual based care” i.e. SFH intervention materials, whereas **Arm 2** consists of “individual based care” plus “supplementary support” i.e. mobile phone text message or letter to smoker(s) at home with an assumption that it would persuade more the smoker to smoke outside the home. As it is a pilot RCT, we aim to recruit 150 newly registered pulmonary TB patients from two selected TB centres with 75 cases in each arm.

**Figure 3 Fig3:**
[figure not shown]
**Trial flow chart.**

#### Inclusion criteria

Should be a registered case of new pulmonary TB, either sputum smear positive or negative ( *new TB patients are defined as those who have no history of prior TB treatment or who received less than 1 month of anti-TB drugs, regardless of whether their smear or culture results are positive or not).*Should be a non-smoker.Have not taken part in a 'Smoke Free Homes’ activity before.Residing within the same district.Aged more than 10 years.Lives with at least one other person who smokes tobacco on a regular basis without any restrictions in the house.

#### Recruitment

The recruitments will start in November 2012 and will continue until we recruit the targeted number of participants. Each participant in the cohort will be followed-up for 6 months after the inclusion in trial. It will be led by the TB facilitator in the TB centre. The following process will be followed to recruit the participants. The TB facilitator will screen all newly registered pulmonary TB patients for inclusion in the trial. The TB facilitator will first confirm that the TB patient is a) case of new pulmonary TB by reviewing the TB register, b) non-smoker by prompting; do you smoke tobacco? such as cigarette, beeri, huqa, cigar, any other (once daily a cigarette/pack, huqa session(s) or any other form of tobacco), c) resident of the same district by reviewing the TB register, and d) aged more than 10 years by reviewing the TB register. All such patients who meet the above criteria and are eligible will be referred to research assistant (RA) for further trial procedures. The TB facilitator will continue offering TB care to all registered patient as per NTP protocol, irrespective of their trial status.

#### Trial registration and informed consent

This will be led by the RA based in the TB centre. The RA will record patient basic information, eligibility and consent. If the patient meets the eligibility criteria the RA will continue with informed consent process.

RA will seek written informed consent from all participants who full fill the eligibility criteria of the trial activities. The RA will use the 'Information Sheet’ to inform the eligible patients about the nature and purpose of the trial; potential risks and benefits of participation in the trial including consequences of participating and not participating in the trial. If the patient does not agree to participate the RA will not proceed with the registration process and will record the reasons for non participation on the specified place in the registration form. The patient will continue TB routine care management at the health facility. We are not offering any personal incentive to the participant for taking part in the study.

#### Patient randomisation

The research team will draw simple randomisation tables where the unit of randomisation will be individuals. The 150 cases will be randomised in to two arms with 75 cases in each arm. The record of randomisation codes and allocation will be maintained by the principal investigator. Once randomised, a participant cannot be withdrawn from the trial. The RA will remain blinded to the fact regarding which arm has been allocated to the patient and will deliver the individual based care to all patients registered in the trial. Once a patient will be registered the information will be send by the RA to the principal investigator who will allocate the arm and inform the co-investigator. The SMS or letter to the arm 2 registered patients will be send by the researcher away from the TB centre. The trial register will be kept in researcher office under lock and key and only the principal investigator will have access to it.

#### Withdrawal

There are possibilities that a patient may decide to discontinue his/her participation in the trial at any stage with or without information. In case, the TB patient discontinues participation in trial during the first month, he/she will be declared non-adherent. Non adherence is defined as any departure from the current approved version of the trial protocol, so that the intervention is not completed. The RA will attempt to retrieve all such patients. In case, the TB patient discontinues participation in trial after the first month, he/she will be declared as 'loss to follow up’. The RA will not attempt to retrieve such patients; however, he will record their TB outcomes at 6 months. The retrieval process will be followed by the TB facilitators as per the TB control protocols. In case, a participant withdraws consent to participate, no further data will be collected from them. However, previously collected data will be used in analyses.

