#### Outcome assessments

All outcomes will be measured after the intervention in each of the study’s arms. The *Primary outcome* will be SFH of non-smoker TB patient by validating through 'Urine Cotinine’ test. During the trial process two urine samples will be collected for cotinine testing at time of registration '0 month’ and at completion of '2 month’ of treatment. The first test will establish the base line where as the test at 2 month will be used to validate the effect of intervention. The urine cotinine testing will be done by the laboratory technician in the TB clinic who will receive relevant training on the conduct of the test and its interpretation. The RA will be kept blinded to the results of urine cotinine and the results will be collected by the researchers directly from the laboratory.

The *Secondary outcomes* will be mainly patient cure rates. All type of patient treatment outcome will be documented including; cured, completed, default, died, failure and transfer out.

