#### Data monitoring

Data will be monitored for quality and completeness by the principal and co-investigator using verification, validation and checking processes. Missing data will be pursued until study end unless they are data obtained by participant contact and this would cause distress.

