#### Data analysis

Summaries of the baseline characteristics of participants will be presented by trial arm, and recruitment and attrition rates will be reported. Although it is a pilot trial and the ample size has not been powered to estimate the likely effect size of the primary outcome, a comparison between the two intervention arms will be undertaken to determine the difference in the outcome between two arms adjusting for health centre. Differences of the secondary outcome between the two arms will also be reported. Analyses will be conducted under the principle of intention to treat, with individual participant as the primary unit of analysis.

### Objective 3

To determine the barriers and key drivers to the creation of smoke free homes. (Phase III).

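### The research assistant stops retrieving participants who discontinue after month 1, although the only post-baseline cotinine sample is due at month 2

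*Protocol article*

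**What the plan says.** The Withdrawal section of the protocol article treats three situations differently.

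- **Discontinuation in month 1.** The participant is classed as non-adherent and the research assistant (RA) tries to retrieve him or her.
- **Discontinuation later** ("In case, the TB patient discontinues participation in trial after the first month"). The participant is classed as lost to follow-up, and "The RA will not attempt to retrieve such patients; however, he will record their TB outcomes at 6 months". The next sentence adds: "The retrieval process will be followed by the TB facilitators as per the TB control protocols".
- **Withdrawal of consent.** "In case, a participant withdraws consent to participate, no further data will be collected from them". Data already collected are kept.

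Under Outcome assessments, "two urine samples will be collected for cotinine testing at time of registration" and again at month 2, and "the test at 2 month will be used to validate the effect of intervention". The TB treatment outcome is the secondary outcome.

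Data monitoring says: "Missing data will be pursued until study end unless they are data obtained by participant contact and this would cause distress". Data analysis says: "Analyses will be conducted under the principle of intention to treat". Patient randomisation adds that nobody can be withdrawn from the trial once randomised. Research questions lists attrition, the likely effect size on the primary outcome, and the feasibility of measuring that outcome among the things the pilot is meant to establish.

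**The concern.** The RA's retrieval effort ends one month before the primary outcome is measured. For a participant who stops taking part in weeks 5 to 8, the RA need only record the 6-month TB outcome, which is secondary. The RA has no duty to secure the 2-month urine sample, which carries the primary comparison. Because withdrawal of consent is a separate case, the rule applies to people who have not refused further data collection.

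Three of the pilot's own questions are affected. Attrition on the primary outcome would partly reflect the retrieval rule and not only participants' behaviour. The effect size carried into the definitive trial would come from those who were sampled. The feasibility of measuring cotinine would be judged under a procedure that stops trying early. In addition, the Objective 3 interviews are limited to patients with a 2-month cotinine result, so anyone not sampled is also lost to the work on barriers.

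**Working it through.** **1. Is there a planned figure to reproduce?** Only the sample size: 2 × 75 = 150, which agrees. The article gives no alpha, power, effect size or dropout allowance and says that the trial is not powered. The main check is therefore one of wording.

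**2. The sections side by side, for a participant who discontinues between months 1 and 2 without withdrawing consent.**

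| Section | What it implies for the month-2 urine sample |
|---|---|
| Withdrawal | No retrieval by the RA; TB facilitators follow TB-care retrieval, urine not mentioned; TB outcome at 6 months recorded |
| Outcome assessments | Sample planned; it is the only post-baseline cotinine value |
| Data monitoring | Missing data pursued to study end, unless obtained by contact *and* the contact would cause distress |
| Patient randomisation | Participant remains in the trial |
| Data analysis | Participant belongs to the intention-to-treat population |

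The Data monitoring exception has two conditions, contact and distress. The Withdrawal rule depends on the calendar alone. For a participant whom contact would not distress, one section requires pursuit and the other tells the RA not to attempt it. That is the direct conflict.

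**3. Who is affected.** Month-1 discontinuers are retrieved by the RA. Those who stop after giving the month-2 sample lose no primary data. People who withdraw consent are outside the rule. That leaves discontinuation between months 1 and 2.

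**4. Illustration of size.** The loss rate d is assumed, because the article gives none. It is the share of each arm without a month-2 sample for any reason, and the rule can account for only part of it.

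- Missing per arm: m = 75 × d, rounded up. Observed: n = 75 − m.
- Width of extreme-case bounds on the difference in proportions (all missing counted as success in one arm and failure in the other, then reversed): 2m/75.
- 95% half-width for the difference at p = 0.5: 1.96 × √(2 × 0.25/n). With no loss this is 1.96 × √(0.5/75) = 16.0 points.

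| d (assumed) | m | n | Bounds width, points | Half-width, points |
|---|---|---|---|---|
| 5% | 4 | 71 | 8/75 = 10.7 | 16.4 |
| 10% | 8 | 67 | 16/75 = 21.3 | 16.9 |
| 20% | 15 | 60 | 30/75 = 40.0 | 17.9 |
| 30% | 23 | 52 | 46/75 = 61.3 | 19.2 |

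Precision changes little. The cost lies in possible bias.

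**5. What unequal loss could do.** If true success is p, a share m of the arm is lost and success among the lost is q, the observed rate is (p − m·q)/(1 − m). Assume p = 0.45 in both arms.

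- Loss 5% v 15%, q = 0.10: 0.445/0.95 = 0.468 v 0.435/0.85 = 0.512, a spurious 4.3 points. With q = 0.20: 0.463 v 0.494, or 3.1 points.
- Loss 10% v 20%: 4.9 points (q = 0.10) and 3.5 points (q = 0.20).
- Swap the loss rates between arms and the sign reverses. With equal loss and equal q the spurious difference is zero.

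**The case against.** Three stronger readings are tempting, and the article does not support them.

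*Late discontinuers are pursued by nobody and their primary outcome is abandoned.* Only the RA stops; retrieval passes to the TB facilitators. Outcome assessments plans two samples without exception, tested by the TB-clinic technician, and nothing forbids sampling a patient who leaves trial activities but still attends for treatment. This part of the objection stands. However, the facilitators' retrieval is governed by TB control protocols. A patient who keeps attending for treatment need not trigger it, and no one is given the task of obtaining the urine sample.

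*The plan contradicts its own intention-to-treat statement.* Intention to treat is stated as an analysis principle. Missing outcomes weaken it, because not everyone randomised contributes a value, but there is no contradiction in words. The textual conflict is with Data monitoring.

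*The comparison is biased towards Arm 2.* A reader might infer this because only Arm 2 sends messages to the smoker, and Ethical considerations concedes that these may cause domestic disturbance. But that section also has the RA check at consent whether such contact would cause problems. The direction depends on which arm loses more people and on how the lost would have fared, and the article gives neither.

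It is also fair to say that this is an unpowered pilot, that the illustrative bias of 3 to 5 points is small beside a half-width of 16 points, and that the handling of missing values is commonly left to an analysis plan not shown here. These points limit the weight of the finding. They do not reconcile the two sections.

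**Conclusion.** The point holds in a limited form. For participants who discontinue between months 1 and 2 without withdrawing consent, the Withdrawal rule allows avoidable missing data on the primary outcome and conflicts with Data monitoring, whose distress exception does not cover a blanket rule by date. The intention-to-treat analysis is weakened, and the pilot's answers on attrition, effect size and feasibility of cotinine measurement are affected.

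Neither the amount nor the direction of any bias can be determined from the article. The 21-point bounds at 10% loss per arm are an extreme case under an assumed rate, and they count all missing samples, not only those due to the rule. This is an inexpensive improvement to a measurement procedure and does not show that the comparison is invalid.

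**What to change.** Reconcile Withdrawal and Data monitoring by replacing the no-retrieval sentence with one to this effect: *the 2-month urine sample will be sought, by the RA or TB-centre staff, from every randomised participant who has not withdrawn consent, whenever he or she discontinued, unless contact would cause distress.* The existing distinction between discontinuing and withdrawing consent can stay. Recording of the 6-month TB outcome is unchanged. The no-retrieval rule should not be carried into the definitive trial.

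Trial status reports that recruitment ended in May 2013, so the last month-2 samples fell due around the end of July 2013, and the new wording cannot recover samples already missed. For those, report the number of missing month-2 samples by arm, describe the primary comparison as based on available samples, and add a bounding sensitivity analysis, for example counting a missing result as a home that is not smoke free (or cotinine unchanged from baseline), together with the extreme cases. Data entry and cleaning were to follow the end of follow-up in November to December 2013, so this could be specified before then.

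The cost is one protocol sentence, a few extra contacts by staff already at the centres, and one added analysis. The downside is a slight burden on participants who disengaged without withdrawing consent.

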#### Data collection

The data will be recorded on trial registration by the RA. The co-investigator will be responsible for maintaining the quality of data collected. A code plan will be prepared to help data entry using SPSS software and the same will be used for analysis.

#### Outcome assessments

All outcomes will be measured after the intervention in each of the study’s arms. The *Primary outcome* will be SFH of non-smoker TB patient by validating through 'Urine Cotinine’ test. During the trial process two urine samples will be collected for cotinine testing at time of registration '0 month’ and at completion of '2 month’ of treatment. The first test will establish the base line where as the test at 2 month will be used to validate the effect of intervention. The urine cotinine testing will be done by the laboratory technician in the TB clinic who will receive relevant training on the conduct of the test and its interpretation. The RA will be kept blinded to the results of urine cotinine and the results will be collected by the researchers directly from the laboratory.

The *Secondary outcomes* will be mainly patient cure rates. All type of patient treatment outcome will be documented including; cured, completed, default, died, failure and transfer out.

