**Methods and design:**

The pilot individual randomised controlled trial of SFH will inform the design of a future definitive trial. We will first develop SFH intervention using taxonomy of behaviour change techniques aimed at encouraging families of non-smoking TB patients to implement smoking restrictions at home following a logic model of the intervention. This will be followed by conducting a pilot randomised controlled trial of intervention within the context of routine TB control programme. The eligible non-smoking TB patients will be randomised and allocated to one of the two trial arms consisting of “individual based care” and “individual based care” plus “supplementary support”. We aim to recruit 150 newly registered pulmonary TB patients from two selected TB centres with 75 cases in each arm. The *Primary outcome* measure will be SFH of non-smoker TB patient by validating through 'Urine Cotinine’ test. We will also determine qualitatively the barriers and key drivers to the creation of smoke free homes followed by developing a definitive trial.

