### Smoking restrictions at home

It is crucial for better health of a family that their home should be free from tobacco smoke, as around 90% of the exposure to SHS takes place at home. This calls for restrictions for smokers to smoke inside the home which could be only achieved by rigorous work by identifying the smoker and convincing him/her not to smoke inside the home thus making a Smoke Free Home (SFH). Factors such as, younger age, being married, dislike for second hand smoke, and personal smoking behaviours such as smoking every day, on occasions, etc were found associated with having home and workplace smoking bans (Heck et al. 2010). In few cases, parents with younger children in home appear to have higher uptake of smoking bans than parents of older children or adolescents (Merom & Rissel 2001; Martinez-Donate et al. 2009). A qualitative study conducted in Scotland revealed that; the enablers to creating smoke free environment within the home include increasing awareness of the risks of SHS particularly in relation to children, desire to be seen as behaving in morally and socially acceptable ways, social norms about the unacceptability of smoking in the home among family and friends including pressure from children. Whereas, the barriers include limited understanding of and resistance to messages about the health risks of SHS, the need to smoke and smoker identity, the home perceived as a private space protected from public controls and sanctions, social norms among family and friends about the acceptability of smoking in the home (Philips et al. 2007). Awareness of the risks of SHS, despite ambivalence about health messages and the fluidity of smoking restrictions provides clear opportunities for public health initiatives to support people attain smoke-free homes.

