#### Research questions

This pilot trial has been designed to answer the following research questions;
What behaviour change techniques are relevant and appropriate to be used in the development of 'Smoke Free Homes’ intervention?What is the feasibility and fidelity of implementing 'Smoke Free Homes’ intervention in TB patients?What is the proportion of non-smoker TB patients among all registered TB cases and what is the smoking behaviour of residents in their homes?What is the rate and reasons of refusal to participate in the research by the non-smokers with smoker in home?What are the recruitment and attrition rates for participants?What is the likely effect size in relation to the primary outcome measure i.e. reduction in the exposure to second-hand smoke validated by a urinary cotinine test after 2 months of TB treatment?What is the feasibility and acceptability of measuring the primary outcome?What are the barriers of change reported by the TB patient during follow-up?What is the feasibility of measuring TB treatment outcomes among trial participants?

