#### Hypothesis

We hypothesis that the SFH educational materials with or without supplementary support (mobile phone text message 'SMS’ or letter to smoker(s) at home on weekly basis) will be effective in relative or absolute reduction of exposure to tobacco smoke at home in non-smoking TB patients living with smoker(s). The option of supplementary support of SMS or letter seems more powerful as this may persuade the smoker at home in implementing smoking restriction in home.

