#### Participants

The participants will be those from which we have received follow-up urine cotinine result i.e. at the end of 2 months of treatment. There will be 12 participants, six from each arm and representing both hospitals and will be grouped as;
Patients who were successful in imposing smoking restriction in their homes.Patients who were unsuccessful in imposing smoking restriction in their homes.Patients who were partially successful in imposing smoking restriction in their homes.

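### The protocol labels two different variables as the primary outcome, smoke-free-home status and reduction in smoke exposure, and its analysis section does not say which is compared

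*Protocol article*

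**What the plan says.** Three places label a primary outcome.

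- Abstract, Methods and design: the primary outcome "measure will be SFH of non-smoker TB patient by validating through" a urine cotinine test.
- Outcome assessments: the same definition, "will be SFH of non-smoker TB patient by validating through" that test. Urine is collected at registration and at 2 months, and "The first test will establish the base line where as the test at 2 month will be used to validate the effect of intervention".
- Research questions: the likely effect size is sought for the "primary outcome measure i.e. reduction in the exposure to second-hand smoke validated by a urinary cotinine test after 2 months of TB treatment".

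Two further places bear on it without carrying the label.

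- Hypothesis: the materials "will be effective in relative or absolute reduction of exposure to tobacco smoke at home in non-smoking TB patients living with smoker(s".
- Data analysis (Objective 2): the two arms are compared on the outcome, adjusting for health centre. Neither the variable nor its type is named.

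Key activities under Objective 4 bases the definitive trial, including its sample size, on the pilot findings.

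**The concern.** Home status is naturally summarised as a proportion. Reduction in exposure is naturally summarised as a mean change or a ratio. A later analysis plan can add detail to a definition, but it cannot honour two definitions that both carry the primary label. The section that could have settled the matter does not.

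Two things are at stake. First, someone holding the data could choose the definition, and then the scale, that looks better. Second, the effect size carried into the definitive trial would depend on which variable was meant.

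There is also a question of fit. Urine cotinine reflects smoke exposure from every place. The Background states that "around 90% of the exposure to SHS takes place at home", so by that figure some exposure arises elsewhere, and a patient whose home is fully smoke-free may still show cotinine. Cotinine therefore measures exposure more directly than it measures the state of a home.

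**Working it through.** **1. The plan's own figure.** Study design and sample gives two arms of 75: 2 × 75 = 150, which agrees. There is no power calculation to reproduce. Data analysis says the size was not powered, and no alpha, effect size, SD or rate is given.

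**2. The definitions side by side.**

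| Place | Variable | Labelled primary? |
|---|---|---|
| Abstract; Outcome assessments | Home status, validated by cotinine | Yes |
| Research questions | Reduction in exposure, by cotinine at 2 months | Yes |
| Hypothesis | Reduction in exposure at home, scale left open | No |
| Data analysis | Not named | Not applicable |

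Two samples are taken, but no rule says whether the variable is the 2-month value or the change from baseline.

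**3. Single patients (assumed values, assumed cutoff of 10).** A fall from 60 to 25 is (60 − 25)/60 = 58% and 35 units, yet 25 fails the cutoff. A fall from 12 to 8 is 4/12 = 33% and 4 units, yet 8 meets it. The first patient does better on reduction, the second on status.

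**4. Whole trials (assumed values).** Cotinine is lognormal with baseline geometric mean 15, log-SD 1.0 and baseline/follow-up correlation 0.6. The follow-up/baseline ratio is 0.8 in one arm and 0.5 in the other. There are 75 patients per arm, tests are two-sided at 5% without centre adjustment, and 1500 trials were simulated for each of the cutoffs 3, 5, 10 and 20.

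| Analysis | Share of trials significant |
|---|---|
| 2-month value below cutoff 3 / 5 / 10 / 20 | 44% / 55% / 65% / 52% |
| Fall of at least 50% | 72-75% |
| Mean log ratio | 89-91% |
| Mean absolute change | 39-42% |

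In 69-77% of trials at least one of the four analyses was significant and at least one was not.

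**5. Effect on the definitive trial (same assumed values).** At any fixed alpha and power, the required size is proportional to the sum of the two arm variances divided by the squared difference.

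- Status below 10, simulated proportions 0.426 and 0.612: (0.426 × 0.574 + 0.612 × 0.388)/0.186² = 0.482/0.0346 = 13.9.
- Log change, variance per arm 2 × (1 − 0.6) × 1.0² = 0.8 and difference ln(0.8/0.5) = 0.470: (0.8 + 0.8)/0.470² = 1.6/0.221 = 7.2.

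The ratio is 13.9/7.2 = 1.9. Here the same underlying effect would call for nearly twice as many patients on the status definition.

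**6. Information kept by a yes/no cut (illustration only).** For a normal outcome cut so that a fraction p lies on one side, relative efficiency is φ(z)²/[p(1 − p)]. At p = 0.5 it is 0.637, and 0.637 × 150 = 95.5. At p = 0.2 it is 0.490, and 0.490 × 150 = 73.5. This assumes a quantitative assay that is roughly normal on the log scale.

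**The case against.** The strongest reply is that this is an explicitly unpowered pilot, with recruitment, attrition and feasibility questions beside the effect size, so no confirmatory claim rests on the choice. Cutoff, scale and variable type are also commonly left to an analysis plan or full protocol that is not shown. Both points stand as far as they go. They do not cover a document that names two different primary outcomes, nor a pilot whose stated purposes include the effect size and the design of the next trial.

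Four stronger readings are tempting, and the documents do not support them.

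- **That there are four competing primary outcomes.** Only two versions carry the label. Participants (Objective 3) does list "Patients who were partially successful in imposing smoking restriction in their homes" beside full success and failure, but those groups serve to choose interviewees: "There will be 12 participants, six from each arm and representing both hospitals and will be grouped as". They show a grading whose rule is not given, not a third outcome. The open scale appears only in the Hypothesis.
- **That relative and absolute reductions may well favour opposite arms.** With equal baseline means, both falls in arm means rank the arms the same way. A reversal needs a baseline gap, as a ratio, larger than the ratio of the two relative falls. A two-fold gap is implausible under randomisation: with log-SD 1.0 (assumed) the standard error of the difference in log means is √(2/75) = 0.163, and ln 2 = 0.693 is 4.2 of these. A small gap can reverse only arms that are nearly tied.
- **That the trial throws away a third to a half of its information.** Yes/no status is implied but never stated, no cutoff is given, and a trained clinic technician runs and interprets the test, so results may come as graded bands. The figures in step 6 would then not apply.
- **That cotinine alone classifies the home.** The text says the status is validated through cotinine, which may mean supporting evidence. The 90% figure is general background, not a property of these patients.

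**Conclusion.** The concern holds in a limited form. The protocol names home status as primary in two places and reduction in exposure in a third. It leaves the scale of reduction open in the Hypothesis and does not resolve the variable in Data analysis. This is a contradiction in the text shown, and it rests on no numerical assumption.

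The definitions can give different answers; the documents hold no data or threshold to show that they will. On one set of assumed values, the share of significant trials ran from 39% to 91% across definitions, and the implied size of the definitive trial differed by a factor of about 1.9. Those sizes would change with the cotinine distribution, the correlation, the cutoff and the assay. Cotinine fits the exposure definition better than the home-status one, which is a reason to prefer the former but does not make the latter unusable.

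**What to change.** Before analysis, name one primary variable and use it identically in the abstract, Research questions, Hypothesis, Outcome assessments and Data analysis. The requirement is a single variable on a single scale.

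The preferred choice is 2-month urine cotinine as a measure of second-hand smoke exposure, analysed on the log scale. Compare the arms as a ratio of geometric means, adjusted for the baseline cotinine already collected and for centre. If the assay returns graded bands, analyse the bands as ordinal. Remove the wording in the Hypothesis that allows either scale of reduction. In Participants, describe the three groups as interview strata only and give the rule that forms them.

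Report smoke-free-home status as secondary only if data on it are already being collected. The article describes no 2-month record of household smoking rules, and recruitment is complete, so new collection should not be part of the required change.

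The cost is wording. Both cotinine samples are already planned, and Trial status places data entry and cleaning after follow-up ends. The downside is a headline that reads as a cotinine ratio, which is less direct for programme readers than a proportion of smoke-free homes.
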